# ParkProTrain: an individualized, tablet-based physiotherapy training programme aimed at improving quality of life and participation restrictions in PD patients – a study protocol for a quasi-randomized, longitudinal and sequential multi-method study

**DOI:** 10.1186/s12883-019-1355-x

**Published:** 2019-06-25

**Keywords:** Parkinson’s disease, Quality of life, Participation, Exercise, Physiotherapy, Telemedicine, App, Tablet

## Abstract

**Background:**

Parkinson’s disease (PD) is one of the most common neurodegenerative diseases. Patients suffer from a variety of motor and non-motor symptoms that severely affect their daily lives and quality of life. In many cases, a three-week inpatient Parkinson’s complex treatment (MKP) can improve the overall condition and quality of life of patients in a short time. In the outpatient sector, however, there is often a lack of human resources and structures necessary for the interdisciplinary treatment of the disease. To support PD patients in continuing the physical exercises they learned from the MKP on a regular basis, a tablet-based training programme will be developed in which exercises can be adjusted to the patient’s abilities. This programme is expected to increase quality of life and social participation, as well as delay the progression of the impairment.

**Methods:**

a) Quasi-randomized, prospective longitudinal study (sequential study design). The intervention group receives a tablet-based training programme during and for 9 months after the MKP, and the control group receives treatment as usual. The evaluation is carried out by means of a written survey at three points in time (the beginning and end of the MKP and after 9 months). b) Qualitative analysis of interviews and focus groups in terms of feasibility and acceptance. c) Formative evaluation of the app and the administration panel. d) Evaluation of the implementation of the training programme by analysing the planned and performed physical activities, as well as evaluation of the phone calls between physiotherapists and patients.

**Discussion:**

The tablet-based training programme can ensure continuous and long-term support for PD patients. They learn different self-management strategies during and after their MKP and are empowered to assume responsibility for carrying out regular physical activity on their own. Because common app stores have no scientifically evaluated apps for PD patients in the German language, the app can fill this gap and help PD patients receive high-quality care in the implementation of physically activating exercises regardless of their place of residence. In addition, the user-centred development of the app ensures that the app meets the specific needs of PD patients.

**Trial registration:**

German Register of Clinical Trials, drks.de. Identifier: DRKS00014952. Registered on June 20th 2018. Date and version identifier April 25th 2019; version 1.

## Background

Parkinson’s Disease (PD) is one of the most common neurodegenerative diseases [1] with an onset usually at 65 to 70 years of age [2]. An increase in the number of affected people is expected [3]. In addition to the serious physical and mental suffering of those patients, the disease represents a heavy financial burden on the German health care system [4], and the total annual costs in Germany are currently approximately 2.8 billion euros [5]. Of this, 70% is attributable to direct medical expenses, which consist of medication costs and inpatient treatment [4]. The number of patients treated with a Parkinson’s complex treatment (Multimodale Komplexbehandlung bei Morbus Parkinson, MKP) according to OPS 8-97d has risen sharply in the last five years [6]. Further costs arise from occupational and physiotherapeutic treatments, among others [7]. Physical activity is of considerable importance to disease progression. Training practices such as physiotherapy and various physical activities (including Nordic walking, Tai Chi, dancing, strength training, treadmill training) have a positive impact on gait, endurance, strength, balance, and quality of life for patients [8–12]. The S3 guideline “Idiopathic Parkinson’s Syndrome” recommends physiotherapy, including other physical activities, as a flexible and long-term treatment strategy. A basic principle is to motivate patients to participate in regular, adaptive physical activity [13]. This is made more difficult not only by motor restrictions (rigor, akinesia) but also by non-motor symptoms. Anhedonia (joylessness), apathy, and possibly depression symptoms often present in many patients are factors that hinder an active lifestyle. The inpatient MKP includes both drug therapy and intensified activating therapy that includes physiotherapy and occupational therapy, among other treatments. MKP improves the overall condition and quality of life of PD patients in many cases [14]. After discharge, however, there is often a lack of the human resources and structures in the outpatient sector that are needed for the necessary interprofessional treatment of the disease [14]. There are almost no physiotherapists with a main focus on PD. Therefore, patients rarely receive PD-specific outpatient physiotherapy care following MKP that builds on the physically activating exercises and on the achieved results of MKP. The aim of this intervention is to achieve largely autonomous initiation and maintenance of physical activity in PD patients.

### Aims

Against this background, patients will receive a tablet-based training programme that is to be used during and after MKP (OPS: 8-97d). The training programme will help PD patients continue the physically activating physiotherapy and other physical activities (such as Tai Chi, Nordic walking, and dancing) that they learned during their MKP. The project has three goals: (1) user-centred development and implementation of an individualized tablet-based training programme, (2) transfer of the physically activating exercises learned in the MKP and other physical activities into everyday life, and (3) improvement in the quality of life and social participation of PD patients and delayed progression of impairment through the regular implementation of the tablet-based training programme.

### Intervention

The planned training programme is based on the HAPA model [15], which focuses in particular on the factors of intent formation and concrete implementation of the established health behaviour. In practice, the patient-centred 5-A-model (assess, advise, agree, assist, arrange) will also be used as an evidence-based framework for health behaviour interventions [16] to increase patients’ self-management skills and support behavioural change [17]. The training programme for PD patients is developed as an application (app). This app will be installed on a tablet, which will be given to the patients of the IG at the beginning of the MKP. The app contains videos with verbal instructions and explanations for all the physically activating exercises taught in the MKP. These exercises are available in different degrees of difficulty and promote endurance, strength and balance. Other physical activities, such as Nordic walking, Tai Chi or dancing, are also suggested. When the patient activates a specific exercise or physical activity, they may also enter personal notes.

During MKP, after completing an exercise, patients record the repetition rate or duration of the exercises on the tablet and rate them with regard to well-being, effort and fun. During the MKP, patients also take part in two patient-centred seminars. The first is primarily for acquiring knowledge and motivation. The focus of the second seminar is on preparing for everyday life at home. Each patient considers personal barriers that may arise in daily routine and strategies to overcome those barriers. Possible action alternatives are defined and entered into the app. At an individual appointment at the end of the MKP, patients plan their personal home training programme on the tablet, with the support of the physiotherapist. The patient chooses exercises that match their abilities, needs and preferences. The physiotherapist assists the patient in putting together their individual training programme: she gives advice regarding the selection of the activating exercises, the degree of difficulty and the number of repetitions. The exercises and the adaptation of the exercises over the weeks are based on the learning method of behaviour shaping in operant conditioning. Here, the desired motor behavioural goal is achieved by gradually increasing effort and difficulty, practising repetitive exercises and constantly adjusting the exercises to the patient’s level of ability. Shaping has proven to be an effective training method in neurological movement disorders [18]. Patients will set a date and time for at least three 30-min sessions of physiotherapy exercises and for at least one physical activity per week for the next three weeks at home. The app displays this individually scheduled training programme in a calendar function. At home, the app reminds patients through a sound signal and/or push notification to execute their exercise programme at the scheduled time. Postponing a session (e.g., due to temporary aggravation of motor impairments, so-called off periods) is possible. The videos offer visual support in the execution of the selected exercises. After completing a scheduled training session, patients will document whether the given repetition number or duration was achieved and whether there were problems performing the exercises, and they also rate the activity in terms of well-being, effort and fun. After the end of the MKP, the data are transferred automatically from the app into an administration panel called “Cockpit” at the clinic. There, the supervising physiotherapist can monitor adherence by controlling the patient’s documentation regarding the execution of the exercises and activities, the repetition number, incomplete video viewings, etc. To permit this, the app transmits the gathered statistics for the activities performed by the patients at regular intervals. To be independent of wireless Internet access, transmission takes place via the mobile network. Based on these data, the physiotherapist provides feedback by phone and adjusts the training programme at regular intervals after the end of the MKP. Because PD patients are prone to small movement amplitudes during exercise that they cannot perceive and therefore cannot correct by themselves, regular correction by experts is required. For this reason, in addition to the telephone contacts, the patients visit the clinic four times after their MKP. Travel expenses to the clinic will be financially reimbursed. If patients have any further need for assistance between those pre-defined appointments, they can contact their physiotherapist at the hospital. Regular, attentive care and feedback from the physiotherapist promote long-term adherence [19].

### App, tablet, administration panel

To ensure the usability and acceptance of the tablet-based training programme and of the administration panel (cockpit), the later users of the system (PD patients, physiotherapists) will be included in the entire development process (User Centred Design, DIN EN ISO 9241-210 [20]). Particular attention will be paid to the skills and abilities of PD patients and to their involvement in the design of the human-technology interface. It was shown in our own studies that interaction with a touchscreen by users with tremor could be significantly improved by appropriate adaptation of the human-technology interface [21, 22]. As part of the user-centred design approach, the design process is initially planned for the first phase, and the usage requirements are specified empirically. In the main phase, design solutions are developed to fulfil these usage requirements. These include (1) the design of the human-technology interface of the tablet-based training programme, (2) the recording and editing of PD-specific support videos for the tablet-based training programme, (3) the design and implementation of the administration panel (cockpit) for the responsible physiotherapist, and (4) the development of telematics connections between the tablets and cockpit, including encrypted transmission and persistent data storage on the clinical server. The solutions will be tested in an iterative formative evaluation and revised if necessary, followed by a final evaluation in the laboratory and possible optimization of the system.

## Methods

### Eligibility criteria

All patients admitted to our partner clinic for a three-week MKP with a diagnosis of idiopathic Parkinson’s syndrome will be eligible to participate (ICD G20.0 and G20.1). Concomitant care and interventions as e.g. privately organized physiotherapy sessions after the MKP are allowed.

Exclusion criteria: Montreal Cognitive Assessment (MoCA) < 18 points, Berg Balance Scale < 41 points, a major depressive episode, moderate to severe dementia, and cardiovascular and orthopaedic/surgical reasons that argue against independent home training. Participants will be also excluded from the study if they are being admitted to an acute hospital during their MKP.

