### Study design

A mixed-methods study [23] with different methodological components will be carried out (sections A-D). The study will be led by the Institute for Social Medicine and Epidemiology of the University of Lübeck. Recruitment will take place at a community clinic in Germany (Neurological Centre, Segeberger Kliniken GmbH in Bad Segeberg). A physiotherapist at this clinic will be in charge of screening the patients for their eligibility within the first three days of their MKP and recruiting them into the study by personally addressing potential participants, giving out the information sheet and collecting the informed consent.

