### Data monitoring

It is a non-drug study investigating the health benefits by a training programme fitted to the individual abilities of the patients. Therefore, harmful or adverse events are not expected. Because it is a study with minimal to no risks, there is no need of a data monitoring committee. An interim analysis is not planned.

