### Case number calculation / sample size

With regard to the changes in the primary outcome, we assume that both groups (the CG and IG) will have improved in a similar way at the end of the MKP. According to our assumptions, the effect of the CG during the subsequent period will approach the starting level again, while the positive changes in the IG will stabilize or even increase slightly. To estimate the required sample size, we have referred to the results of existing studies on the influence of physical activity on quality of life (PDQ-8) in PD patients. For the effect determination, the data of Ebersbach et al. [46], Morris et al. [47] and Nadeau et al. [10] are being consulted. In Ebersbach et al., the quality of life over a 4-month course showed effect sizes of average magnitude (ES = 0.47) for patients who underwent physical training (Nordic walking), whereas there was no change in the CG. Morris et al. also report a significantly improved quality of life, with a mean effect size of ES = 0.45, after muscle training over a 3-month span. In their controlled study on the effect of intensive treadmill training (speed and incline) on quality of life, Nadeau et al. found an effect size of ES = 0.73 over a 6-month course; for simple treadmill training, they found an effect strength of ES = 0.21. In the CG, the quality of life did not change. For the calculation of the number of cases, we assume that participation in the tablet-based training programme (IG) will lead to clinically relevant positive effects (t_0_ vs. t_2_ ES = 0.40) on quality of life (PDQ-8) 9 months after the end of MKP. In contrast to the IG, there will be no changes in the CG at t_2_. To demonstrate differences between the IG and CG 9 months after MKP on the order of at least ES = 0.4 with two-sided testing at α = 5% and a power of 80%, a group size of *N* = 100 net is required for each IG and CG. We expect only a moderate dropout rate of 25% among patients after MKP due to their attachment to the clinic. Thus, to be able to evaluate N = 100 patients per group, 133 participants per study group must initially be included. Approximately 120 PD patients participate in the MKP per quarter at the partner clinic. Based on the defined inclusion and exclusion criteria, we expect 70 patients per quarter to be included in the study. The recruiting of the CG and IG will take place over a period of nine months each. Taking into account a rate of study refusal of 25%, the targeted number of cases in the clinic can be recruited within this time frame.

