
## Statistical methods

### Quantitative analyses

Repeated analysis of variance will be used to analyse the longitudinal data, a contingency table analysis will be used for nominal and ordinal parameters, and chi-square tests and t-tests will be used for subgroup analysis. Subgroup analyses are planned for age, sex and education (boundaries: high vs. low). For the evaluations only complete cases are used. The analyses will be performed using the statistics programme SPSS 22.0.

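### Participants admitted to an acute hospital during the MKP are excluded after enrolment and assignment, which can bias the group comparison in either direction and takes patients with possible early harm out of follow-up

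*Protocol article*

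**What the plan says.** Under Eligibility criteria, after the list of baseline exclusions, the protocol article adds: "Participants will be also excluded from the study if they are being admitted to an acute hospital during their MKP". The sentence concerns people who are already participants, and the event can occur at any time in the three-week stay.

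The timing comes from other sections:

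- **Enrolment.** Study design puts a physiotherapist in charge of "screening the patients for their eligibility within the first three days of their MKP" and of obtaining consent.
- **Assignment.** Section A (quantitative measures) assigns by recruitment period, first the CG and then the IG. Nobody is blinded.
- **Start of the intervention.** The Abstract states: "The intervention group receives a tablet-based training programme during and for 9 months after the MKP". The Intervention section says: "This app will be installed on a tablet, which will be given to the patients of the IG at the beginning of the MKP". It also describes use during the stay: "During MKP, after completing an exercise, patients record the repetition rate or duration of the exercises on the tablet". Two seminars take place during the stay as well.

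Three further statements determine what happens to an excluded patient:

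- **Analysis set.** Quantitative analyses: "For the evaluations only complete cases are used".
- **Hospital stays.** Table 1 collects these under use of health services, at t0 and t2 only.
- **Harms.** Data monitoring: "Therefore, harmful or adverse events are not expected". No monitoring committee is planned.

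**The concern.** An eligibility criterion should be decidable before a patient is assigned. This one depends on an event that happens afterwards, and in the IG usually after exposure has started. The groups analysed are then no longer all the patients assigned, but those assigned who were not transferred out.

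Two things are at stake. First, the primary comparison at t2 is conditioned on a post-assignment event. If that event is more common in one group, or affects patients with a different prognosis, the contrast moves. The groups come from successive periods and nobody is blinded, so a difference could come from the intervention, from calendar time, or from how transfers are decided and recorded. Second, an IG patient who comes to harm early and is transferred leaves the study, and none of the outcomes described would capture the event. That matters in a study whose safety position is that no harm is expected.

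**Working it through.** **Sequence of events**

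1. Days 1–3 of the MKP: screening, consent, and assignment by recruitment period.
2. Start of the MKP, IG only: tablet handed over; app recording and seminars follow during the stay.
3. Any time up to the end of the stay: acute admission leads to exclusion from the study.
4. t1 at the end of the MKP; t2 nine months later.

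Step 3 comes after step 1 for most of the stay, and generally after step 2 in the IG. An excluded patient does not reach t2, so the Table 1 item on hospital stays cannot pick up the admission. Restricting the analysis to complete cases does nothing to bring the patient back.

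**Plan's own figures**

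Inputs from the sample size section: ES = 0.40, two-sided α = 5%, power 80%, 25% dropout. A two-sample t-test needs 99.08 per group, in line with the stated 100. Inflation gives 100 / 0.75 = 133.3, in line with the stated 133.

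**Size of a possible bias**

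The document gives neither an admission rate nor the prognosis of those admitted, so every input here is an assumption. Let p be the proportion removed from a group and D how much worse, in SD, the removed patients would score at t2 than those who stay. Removal makes that group's mean look better by p × D. The contrast shifts in favour of the IG by

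shift = p(IG) × D(IG) − p(CG) × D(CG).

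| p(IG) | p(CG) | D(IG) | D(CG) | Shift towards IG (SD) | Share of 0.40 |
|---|---|---|---|---|---|
| 5% | 5% | 0.8 | 0.8 | 0.04 − 0.04 = 0 | 0% |
| 5% | 2% | 0.8 | 0.8 | 0.04 − 0.016 = 0.024 | 6% |
| 5% | 0% | 0.8 | 0.8 | 0.04 − 0 = 0.04 | 10% |
| 2% | 5% | 0.8 | 0.8 | 0.016 − 0.04 = −0.024 | −6% |
| 5% | 5% | 1.0 | 0.5 | 0.05 − 0.025 = 0.025 | 6% |
| 10% | 2% | 1.0 | 1.0 | 0.10 − 0.02 = 0.08 | 20% |

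The sign follows whichever group loses more, or sicker, patients. The last row is a deliberately extreme case.

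**Numbers available**

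Section A recruits each group until the target is reached. The sample size section expects 70 eligible patients per quarter for three quarters and 25% refusal: 70 × 3 × 0.75 = 157.5 per group, against 133 needed. Keeping 133 after a 5% removal takes 133 / 0.95 = 140 enrolled, and after 10% it takes 133 / 0.90 = 148. Both fit.

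**The case against.** The strongest reply is that the rule applies equally to both groups and that little separates them during the stay. The app shows the exercises taught in the MKP, which both groups receive, and treatment is documented to check equal handling. What the IG receives in addition is the app, the seminars and a planning appointment at the end. Home training starts after discharge, when the rule no longer acts. The question is whether MKP gains are maintained, so restricting to patients not transferred out could be called a sensible target population. Some admissions may also precede tablet handover.

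Much of this stands. It keeps the likely bias small and leaves its direction open. It does not make the rule harmless: the intervention period includes the MKP, assignment precedes the event, and sequential recruitment allows admission rates to differ for reasons unrelated to the app. The Limitations section proposes covariates or propensity score matching for differences in patient characteristics, but adjusting for baseline differences does not in general undo selection on a later event.

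Three stronger readings are tempting and not supported:

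- **That the exclusion favours the IG.** This needs more admissions, or worse prognosis among those admitted, in the IG. The document gives no reason to assume either.
- **That power falls.** The dropout allowance is indeed defined for the time after discharge: "We expect only a moderate dropout rate of 25% among patients after MKP due to their attachment to the clinic". If recruitment stopped at 133 and 5% were removed, 133 × 0.95 × 0.75 = 95 would remain, with about 78% power. But recruitment runs to target and the window has room for replacements. Replacement restores the number of patients, though not the comparability of the groups.
- **That transfers go unrecorded.** Patient flow in the clinic is documented. What is lost is follow-up and any outcome that captures the event.

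**Conclusion.** The point holds as a stated rule that conditions the comparison on an event after assignment. It is not a detail left to a fuller document: exclusion from the study ends follow-up, and an analysis plan cannot recover t2 values that were never collected.

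The numerical effect is probably small. It is zero if admission rates and prognosis are the same in both groups, and about 0.02–0.04 SD under assumed rates of 5% against 0–2% with outcomes 0.8 SD worse. It could run either way. The loss of follow-up on IG patients with possible early harm does not depend on the rates being unequal. It is limited to the inpatient weeks, since nobody is removed by this rule after discharge. The case for changing the rule rests on the validity of the as-assigned comparison and on harm information, not on power.

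**What to change.** 1. Delete the sentence as an exclusion criterion. State that every consenting enrolled patient stays in the analysis of the assigned group.
2. Send the t1 and t2 questionnaires to transferred patients where possible.
3. Report acute admissions during the MKP by group, with reasons.
4. Amend the complete-case rule under Quantitative analyses so that the primary t0-to-t2 comparison keeps patients who lack only t1. A mixed model for repeated measures would do this, as would t2 adjusted for t0. Neither is in the present plan, and without this step a retained patient with no t1 value could still be dropped from the repeated analysis of variance.
5. Keep the analysis without transferred patients as a sensitivity analysis. It answers the narrower question about those who completed the stay.

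The cost is a change of wording, a few extra questionnaires and some missing t1 values. The change concerns study follow-up and analysis only, not how transferred patients are treated.
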